#### Secondary Objectives

Secondary objectives will include: 1) assessment of satisfaction, usability, and acceptance of the intervention (tools); 2) evaluation of the cost-effectiveness of the intervention; and 3) evaluation of changes in health care consumption. Objective #1 will be achieved through validated questionnaires and qualitative interviews with end users and their caregivers (if applicable) and objective #2 will be evaluated using standardized and validated questionnaires only (Table 1). Objective #3 will be assessed using a purpose designed questionnaire.

#### Exploratory Objectives

The current trial will also cover a number of exploratory objectives where the focus will be on 1) identifying subgroups of patients who might benefit the most from this intervention based on their profile (eg, psychological and/or disease profile); 2) evaluating the effects of the intervention on the electrocardiogram (ECG) data; and 3) gaining more insight in patients sleep patterns and physical activity over a prolonged period of time. These objectives will mainly serve the development of our new hypothesis regarding successful lifestyle change and will be tested using latent class analysis (LatentGold 5.0).

### Intervention Versus Care as Usual

#### Intervention

The Do CHANGE intervention consists of different components, which can be used to provide care that meets patients’ needs. All patients included in the intervention group will be provided with the following technology: CarePortal, Moves app, Do Something Different (behavioral program), Beddit, Fitbit, blood pressure monitor, COOKiT, and Vire (the Do CHANGE app). In addition, disease-specific tools will only be provided to those who need them (ie, weight scale and/or FLUiT). Based on patients’ primary diagnosis (HF, CAD, or HT) the tools that might be useful will be recommended by the cardiologist. For example, patients with HF will receive a weight scale, since this can assist with monitoring sudden weigh gain, which might be an indication of deteriorating cardiac function. Figure 2 provides a schematic overview of the intervention components. To decrease patient burden, the COOKiT and FLUiT will be introduced to patients two months postbaseline measurement.

#### Do Something Different

All patients randomized to the intervention group will receive the DSD program, which has previously been developed to change behavioral habits and flexibility [13]. For the current trial, the program has been adapted to cardiac patients’ needs and profiles to meet the lifestyle recommendations of this specific population.

The program challenges patients to step out of their comfort zone by sending behavioral prompts (Do’s) such as “Explore more today instead of going the same old way, take a different route. Look around, spot ten things you wouldn't see on your usual journey.” By breaking the old unhealthy habits, patients are expected to be more flexible and able to change their behavior. The program aims to change behavioral habits, increase flexibility, and subsequently change habits associated with an unhealthy lifestyle and distress, which are both found to be associated with hypertension and cardiovascular risks. “Typical” behavioral risks have been identified and are addressed within the program. To further adapt the program to patients’ needs, all patients, prior to starting the program, will be assessed regarding their daily functioning, distress, and personality such that the Do’s will match their personal (unhealthy) habits and challenge them to change.

After assessing patients’ personality profile, the intervention will be provided for 11 weeks. Patients will receive a total of 32 Do’s messages during this period. Also, 16 ToDo’s will be delivered to the patients based on their current functioning (eg, if a patient is not performing sufficient exercise, based on the Fitbit data, he/she will receive a Do based on that). Patients will receive their Do’s and ToDo’s through the care portal, the Do CHANGE app and via short message service, depending on patients’ preferences.

The intervention group will also receive some devices which will help them to monitor their health behaviors and give them some insight into their daily functioning. These devices will include:

##### CarePortal

The intervention group will also receive a CarePortal (Docobo Ltd), which will be installed at their home. The CarePortal is a clinically certified portable device that will allow the patients to monitor their disease symptoms on a daily basis (ie, by answering a set of predefined questions every day) and send these outputs to a health care professional (cardiologist). The CarePortal will be used to gather ECG data, symptomatic data, blood pressure, and weight on a daily basis. The patient will be able to take the ECG measure at any time. By touching the screen of the CarePortal, the instructions to take the measurement will appear, guiding the patient step by step to take the ECG (which will take 2 minutes). The CarePortal will send the physiological data directly to the cardiologist, who will be able to view them via an online platform and contact the patient if necessary. Also, the patients will see their data (the same data their cardiologist will receive) over a period of 6 months by accessing the online patient portal.

##### Beddit

To objectively log patients’ sleep data and evaluate whether their sleep pattern has changed over time, patients assigned to the intervention group will all receive the Beddit device [16]. Beddit is a certified device to measure sleep, heart rate, and breathing during time spent in bed. The device has been validated [17] and is considered one of the most accurate devices to monitor sleep. For the current trial the Beddit 3 will be used.

##### Fitbit

Patients’ physical activity will be assessed using the Fitbit “Alta HR” [24]. The Fitbit Altra HR is a European Conformity (CE-Marked) activity tracker and can be worn on the wrist. With the Fitbit, patients’ step count, the intensity of physical activity, heart rate, calories burned and distance walked will be assessed. Data from the Fitbit will also be used to initiate ToDo’s.

##### Blood Pressure Monitor

All patients in the intervention group will receive the digital blood pressure monitor, UA-767 Plus, which is a CE-Marked medical device. Patients will be asked to measure their blood pressure on a daily basis and log the blood pressure values through the CarePortal.

##### COOKiT

COOKiT is a smart spatula that can monitor patients’ cooking behavior (through a motion sensor which indicates whether the spatula is used) and measure the salinity—for both sodium and potassium—of the food that is prepared. The COOKiT has been developed within Do CHANGE and will be provided to patients two months postbaseline measurement.

**Figure 2 figure2:**
[figure not shown]
Schematic overview of the Do CHANGE intervention components.

##### Vire (Do CHANGE App)

In order for patients not to feel overwhelmed by the apps and devices that they will have to check every day (if they are interested in their progress), the Vire app (Do CHANGE app) has been developed as the integration point. The Vire app was developed together with end users and health care professionals to provide an overview of the data gathered by all the devices that the patients will be using during the study (eg, Beddit, Fitbit, COOKiT, etc). Through this application, patients will also be able to receive the Do’s from the DSD program. In addition, patients will be asked to take pictures (at least 3 per day) of the food which they have consumed each day (via this app). These images will automatically be sent to the health care professional portal (which is also linked to the CarePortal) such that the health care professional will be able to see what the eating habits of the patients are.

##### Moves App

Moves app is an activity and global positioning system tracking application installed on the mobile phone. The app helps to provide information useful for assessing the behavioral indicators—social opportunity, variety, and activity—used for generating ToDo’s. All patients participating in the intervention will have to install the Moves app on their mobile phone.

#### Additional Devices

Dependent on the primary diagnosis, the patient will decide together with the health care professional which of the following, additional devices they will be using:

##### FLUiT

Particularly for patients with HF the FLUiT will be recommended. FLUiT is a newly developed device in Do CHANGE which can measure fluid intake. FLUiT is a “smart sleeve” which can be wrapped around a cup, bottle or glass, and will gauge the amount of fluid that it contains. It comprises of an accelerometer and a touch sensor to detect when actual drinking occurs and will log the quantity drank. FLUiT will be provided to patients two months postbaseline measures.

##### Weight Scale

Patients with HF will be provided with a weight scale to monitor their weight on a daily basis. For the current trial, the Seca Aura 807 model will be used. Patients will be able to communicate their weight on a daily basis by answering the question on the CarePortal.

Patients will all be monitored weekly via telephone to make sure that they are compliant with the program. During these phone calls, patients will also receive feedback on their eating habits.

### Care as Usual

Patients who are randomized to the comparator group will receive care as usual. There will be no restrictions on this group. Patients in this condition are allowed to seek additional care and also use other tools, which will enhance their disease and well-being, provided that they report this in the purpose designed questionnaires at follow-up.

### Statistical Analyses

Data will be analyzed using SPSS (IBM statistics 22) and LatentGold (Version 5.0) [24,25] statistical package. Continuous and discrete variables will be compared using respectively Students’ t-test and Chi-square test. The Linear Mixed Models (LMM) procedure will be performed to evaluate the treatment effectiveness over time. The LMM procedure is similar to linear regression analyses except that in LMM the dependent variable is measured at multiple time points. These analyses will be adjusted for baseline distress levels. If the interaction effects are not significant, only the main effects will be entered in the final model. To examine which patients might benefit from the intervention based on their profiles, Latent Class Analyses will be performed [26,27]. An alpha of .05 will be used to indicate level of significance.

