**Results:**

The Do CHANGE trial will provide us with new insights regarding the effectiveness of the proposed intervention in different cultural settings. In addition, it will give insight into what works for whom and why.

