### Sample Size

A total number of 250 patients will be enrolled in the study at three participating centers (Badalona Serveis Assistencials, Badalona, Spain [N=75]; Buddhist Tzu Chi Dalin General Hospital, Dalin, Taiwan [N=100] and Elisabeth-TweeSteden Hospital, Tilburg, The Netherlands [N=75]). The sample sizes were determined based on the number of patients visiting the outpatient clinic per center.

One hundred and twenty-five patients will be enrolled in the intervention group and 125 in the control group. Considering participation rates in the previously performed Do CHANGE trial and other randomized controlled trials, we expect a significant number (50%) of patients to refuse participation. Hence, we will need to approach 500 patients. As the current trial aims to provide a proof of concept, sample size calculation will not be performed. A total of 250 patients is considered sufficient to meet this purpose.

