## Discussion

Cardiovascular diseases are the leading cause of death globally, and they pose a significant burden on current health care systems [1,28]. Studies have shown that behavioral factors (eg, physical inactivity, unhealthy diet) account for a large proportion of the disease burden and thus should be addressed (potentially) by health care providers [2]. The Do CHANGE trial aims to address lifestyle behaviors and increase the quality of life of patients with CAD, HF, and HT. By increasing patients’ behavioral flexibility and providing them with supportive devices, patients are expected to break with their unhealthy habits and change their unhealthy lifestyle in a sustainable manner.

According to Pine & Fletcher [13] there are multiple reasons why current behavioral programs have not been successful in changing health behaviors. Firstly, our behavior is only partly guided by willpower, hence, most patients fail to use willpower to prevent habitual behaviors (eg, smoking). Secondly, behavior is often guided by everyday environmental cues which trigger certain response (eg, having a beer triggers smoking). Finally, there is a knowledge-doing gap which is demonstrated by the fact that we often know what is good for our health but we fail to do it [12,13]. People tend to live by their habits, which can be stable over time, and seem not to be able to act in accordance with their knowledge. Hence, within Do CHANGE, we aim to increase awareness and knowledge about unhealthy behaviors and at the same time, by using the DSD technique, disrupt habit chains in daily living. This is expected to boost behavioral flexibility and enhance behavior change [15].

A total of 250 patients will be recruited from three pilot sites (Spain, The Netherlands, and Taiwan) and will be randomized to either the intervention group or care as usual. Patients in the intervention group will receive the DSD program (for three months) and will be using devices that will assist them in behavior change (for 6 months). Patients will be assessed at baseline, and at the third and sixth months.

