The current trial might face some challenges due to the international scope and the number of devices that are given to patients. As patient recruitment will take place in Spain, The Netherlands, and Taiwan, cultural differences might affect the outcomes of the trial. Also, due to logistical differences between the pilot sites, patient recruitment will be slightly different per site. Although we do not expect this to have a significant impact on the results, we do consider it as a challenge. Secondly, some patients will receive multiple devices and/or apps that they are expected to use for 6 months. This might be perceived as overwhelming and may potentially lead to lower adherence. However, the current trial implements a behavior change component to the intervention, which aims to increase personal flexibility and enables behavior change. This might lead to more openness for new behaviors (using devices) and thus improve adherence.

Do CHANGE will provide insights into lifestyle changes and the possible mechanism that might drive this change. In addition, it will give valuable information from objective measures about patients’ behavioral patterns which, in turn, could serve as input for future studies that will focus on personalized medicine. This information will also provide input for the development of future ecological momentary interventions (real time interventions) that are focused on providing care to patients whenever and wherever they prefer it.

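### The stated mixed model names baseline distress as its one adjustment variable, leaves the role of month 0 open, and specifies no country or treatment-by-country term despite the cultural-settings aim

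*Protocol article*

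**What the plan says.** The Protocol article sets out the effectiveness model under Statistical Analyses: "The Linear Mixed Models (LMM) procedure will be performed to evaluate the treatment effectiveness over time". It describes the method this way: "The LMM procedure is similar to linear regression analyses except that in LMM the dependent variable is measured at multiple time points". Two further sentences fix its content: "These analyses will be adjusted for baseline distress levels" and "If the interaction effects are not significant, only the main effects will be entered in the final model". No other covariate is named, and the article does not say which interactions are meant.

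On timing, the Discussion states: "Patients will be assessed at baseline, and at the third and sixth months". Table 1 marks months 0, 3 and 6 for the lifestyle, flexibility and quality-of-life questionnaires. Nothing says whether month 0 is one of the modelled responses.

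On country, the Results paragraph of the abstract says: "The Do CHANGE trial will provide us with new insights regarding the effectiveness of the proposed intervention in different cultural settings". The Discussion adds that "cultural differences might affect the outcomes of the trial". Under Sample Size the three centers, one per country, contribute 75, 100 and 75 patients, with 125 per arm. Those numbers come from clinic volume ("The sample sizes were determined based on the number of patients visiting the outpatient clinic per center"), and no power calculation is made.

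**The concern.** The article commits to an adjustment set and to a rule for removing interactions, so both can be judged as they stand. Three things look weak.

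- **Baseline.** The outcome's own month 0 score is collected on every patient and would normally predict follow-up well, yet it is not named as a covariate. Distress does not stand in for it. If month 0 is a response and data are complete, a time-constant distress effect cancels out of the arm-by-time contrast and adds nothing to its precision.
- **The drop rule.** If month 0 is a response and the arm-by-time interaction is removed, the remaining treatment main effect averages all three visits, one of which precedes treatment.
- **Country.** The article says culture may influence outcomes and promises insight by setting, but the model has no country term and no treatment-by-country term. The only analysis of who benefits is the latent class analysis, which is described in terms of patients' psychological or disease profile, not country.

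At stake are precision in a trial that did not calculate its sample size, a treatment estimate that may be diluted by the model-reduction rule, and a stated aim without a specified analysis.

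**Working it through.** **Inputs from the article.** 125 per arm; 75, 100 and 75 per country; alpha 0.05; visits at months 0, 3 and 6.

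**Assumptions, because the article gives none of these.** Two-sided test, 80% power, SD = 1, equal correlation r between any two visits (0.3 to 0.8), complete data, a constant effect of 0.30 SD at months 3 and 6, and country explaining a share R² of 0.02 to 0.15 of residual variance.

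**The article's own figures.** 75 + 100 + 75 = 125 + 125 = 250, and 250/(1 − 0.5) = 500 to approach. Both reproduce.

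**1. Role of month 0.** The variance of the arm difference at one visit, in units of 2/125 = 0.016, is:

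- month 0 unused: 1
- month 0 as a free response, arm-by-time contrast: 2(1 − r)
- month 0 as covariate, or arms constrained equal at month 0: 1 − r²

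The third divided by the second is (1 − r²)/(2(1 − r)) = (1 + r)/2. The detectable difference is (1.960 + 0.842) × √variance; with month 0 unused this is 2.802 × √0.016 = 0.354 SD.

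| r | Unused | Free response | Covariate or constrained | Variance ratio (1 + r)/2 |
|---|---|---|---|---|
| 0.3 | 0.354 | 0.419 | 0.338 | 0.65 |
| 0.5 | 0.354 | 0.354 | 0.307 | 0.75 |
| 0.6 | 0.354 | 0.317 | 0.284 | 0.80 |
| 0.7 | 0.354 | 0.274 | 0.253 | 0.85 |
| 0.8 | 0.354 | 0.224 | 0.213 | 0.90 |

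At r = 0.5, 0.6 and 0.7 the ratio is worth 1/0.75 − 1 = 33%, 1/0.80 − 1 = 25% and 1/0.85 − 1 = 18% more patients. Below r = 0.5 the free-response contrast is less precise than ignoring month 0 altogether.

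**2. Dropping the interaction with month 0 as a response.** The main effect estimates (0 + 0.30 + 0.30)/3 = 0.20 SD, a loss of one third. Its variance is 0.016 × (1 + 2r)/3. A constrained model that averages months 3 and 6 estimates 0.30 SD with variance 0.016 × [(1 + r)/2 − r²]. At r = 0.6:

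- main effect: 0.016 × 2.2/3 = 0.01173, SE 0.108, power 0.455
- constrained: 0.016 × 0.44 = 0.00704, SE 0.084, power 0.947

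From r = 0.3 to r = 0.8, power runs from 0.58 down to 0.40 for the main-effects model and from 0.89 up to 0.996 for the constrained model. If only months 3 and 6 are responses, dropping the interaction does not dilute the effect.

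**3. Country as a fixed effect.** The standard error is multiplied by √(1 − R²): 0.990, 0.975, 0.949 and 0.922 for R² = 0.02, 0.05, 0.10 and 0.15. This applies to comparisons not made within patients. A constant country difference cancels in a change-score contrast.

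**4. Effects by country.** Within one country the detectable effect is 2.802 × √(2/37.5) = 0.65 SD for 75 patients and 2.802 × √(2/50) = 0.56 SD for 100. For a difference in effect between two countries the variance is 4/Nₐ + 4/N_b:

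- 75 against 75: 2.802 × √0.1067 = 0.91 SD
- 75 against 100: 2.802 × √0.0933 = 0.86 SD

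With baseline as a covariate at r = 0.6, both are multiplied by √(1 − 0.36) = 0.8, giving 0.73 and 0.68 SD.

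**The case against.** The strongest reply is that a journal article condenses. Covariate lists, site terms and the coding of month 0 often sit in an analysis plan, and naming one covariate does not make the list exhaustive. A change-type contrast is valid under randomization, so its cost is efficiency, not bias. The trial calls itself a proof of concept, and its listed primary, secondary and exploratory objectives contain no between-country comparison.

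Much of this stands, and it rules out three stronger readings that a reader might infer.

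- **That the outcome's baseline is left out of the model.** The response is measured at several time points and the visits include month 0, so baseline may already be in the model as a response. The text does not settle it.
- **That the cultural-settings question cannot be addressed.** The unnamed interactions could include country, and per-country estimates need no prespecified test. The article merely specifies no analysis that does this.
- **That randomization ignores country.** The Randomization section does not mention stratification. Silence there is not evidence of a fault, and no change to the allocation lists follows from it.

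The reply does not remove the point. At r of 0.5 to 0.7, either reading of month 0 is less precise than covariate adjustment. The interaction rule is a written commitment. Applied to a treatment-by-country term, it would usually delete that term, since only large differences are detectable.

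**Conclusion.** The concern holds as a weakness in the stated model, not as an error that invalidates it. Three parts stand.

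- **Baseline.** With month 0 as a free response, the variance of the arm contrast could be cut to 75%, 80% or 85% at assumed correlations of 0.5, 0.6 or 0.7. With month 0 unused, the loss at these correlations is equal or larger. The gap narrows as the correlation rises.
- **Drop rule.** This is the most consequential part, but it is conditional: if month 0 is a response and the arm-by-time interaction is removed, a constant effect is diluted by one third.
- **Country.** No specified term serves the cultural-settings aim. The precision gain from a country term is modest, about 1% to 8% of the standard error for R² of 0.02 to 0.15, and it vanishes in within-patient contrasts. The main reason to include country is the aim itself, and at this size the result would be descriptive.

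The correlations, the R² values and the 0.30 SD effect are assumptions. The one-third dilution also assumes equal correlation between visits and complete data.

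**What to change.** Amend the model description under Statistical Analyses as follows.

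- Model months 3 and 6 as responses with the outcome's own month 0 value as a covariate, or keep month 0 as a response with the arms constrained to be equal there. State which.
- Add country as a fixed effect and keep baseline distress.
- Report the treatment contrast at months 3 and 6 whatever the interaction test shows, so that the removal rule never produces an effect averaged over month 0.
- Report treatment-by-country estimates with confidence intervals, labelled exploratory, with no significance claim for any single country.

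The outcome baselines and distress are already measured, and country is known from the center. The cost is a few lines of text and a few degrees of freedom.
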